## Abstract

**Background:**

Acute lung injury occurs in approximately 25% to 30% of subjects undergoing oesophagectomy. Experimental studies suggest that treatment with vitamin D may prevent the development of acute lung injury by decreasing inflammatory cytokine release, enhancing lung epithelial repair and protecting alveolar capillary barrier function.

**Methods/Design:**

The ‘Vitamin D to prevent lung injury following oesophagectomy trial’ is a multi-centre, randomised, double-blind, placebo-controlled trial. The aim of the trial is to determine in patients undergoing elective transthoracic oesophagectomy, if pre-treatment with a single oral dose of vitamin D_3_ (300,000 IU (7.5 mg) cholecalciferol in oily solution administered seven days pre-operatively) compared to placebo affects biomarkers of early acute lung injury and other clinical outcomes. The primary outcome will be change in extravascular lung water index measured by PiCCO® transpulmonary thermodilution catheter at the end of the oesophagectomy. The trial secondary outcomes are clinical markers indicative of lung injury: PaO_2_:FiO_2_ ratio, oxygenation index; development of acute lung injury to day 28; duration of ventilation and organ failure; survival; safety and tolerability of vitamin D supplementation; plasma indices of endothelial and alveolar epithelial function/injury, plasma inflammatory response and plasma vitamin D status. The study aims to recruit 80 patients from three UK centres.

**Discussion:**

This study will ascertain whether vitamin D replacement alters biomarkers of lung damage following oesophagectomy.

**Trial registration:**

Current Controlled Trials ISRCTN27673620

## Background

Acute lung injury (ALI) and the more severe acute respiratory distress syndrome (ARDS) are common, devastating clinical syndromes of acute respiratory failure in the critically ill person. The incidence of ALI is 79 per 100,000 person years with a mortality rate of 30% to 65% [1]. Survivors of ARDS experience a significant reduction in health-related quality of life, with 46% reported to be unable to return to work within 12 months.

ALI is the final common pathway of response to a variety of direct pulmonary insults, such as bacterial /viral pneumonia and gastric aspiration, or indirect insults, such as abdominal sepsis or battlefield trauma. Only a relatively small proportion of patients develop ALI, with research suggesting that genetic, demographic (age), social (smoking, alcohol abuse) and other factors play a role in determining who develops ALI [1,2]. There are no current readily available tests that can clearly identify those who are at high risk of ALI and no therapeutic interventions proven to prevent its occurrence.

### One lung ventilation (OLV) as a model for ALI/ARDS

To allow access to the oesophagus during surgery (using the transthoracic technique), one of the lungs is deflated and the subject is ventilated through the other lung. This is known as one-lung ventilation (OLV). There is a high postoperative incidence of ALI/ARDS [3-5] following OLV and unlike most insults leading to lung injury the delivery of OLV is predictably timed, thereby allowing serial studies to be carried out throughout the period of stimulus and development of the condition. Preoperative risk factors including age, respiratory function and cigarette smoking have been found to be related to the incidence of postoperative pulmonary complications [3,6-8]*.* It is unclear at present why only a percentage of patients undergoing OLV develop lung injury or why the lung injury typically occurs 24 to 48 hours after the cessation of OLV. Our data show that the development of lung injury is, however, associated with a doubling of in-hospital stay and elevated mortality.

We have extensively modeled the local and systemic inflammatory response to transthoracic oesophagectomy in 50 patients undergoing OLV. After OLV, patients have a neutrophilic alveolitis, with a significant alveolar and systemic inflammatory response. This is associated with the release of markers of both endothelial and alveolar epithelial dysfunction and an increase in the permeability of the alveolar barrier. This manifests clinically as increased extravascular lung water and a fall in oxygenation.

Alveolar levels of surfactant protein D and bronchoalveolar lavage fluid (BALF) protein permeability index are highest in those who develop ALI within 72 hours of OLV suggesting that peri-operative alveolar epithelial damage is a risk factor for the subsequent development of ALI. Immediate post-operative plasma markers of neutrophilic activation (myeloperoxidase, and matrix metalloproteinase-9 (MMP-9)) as well as the receptor for advanced glycation end-products (RAGE, a type I epithelial cell marker) are similarly raised in those who develop ALI within 72 hours of OLV. Proposed causative mechanisms for this injury include the ischaemic/reperfusion insult suffered by the collapsed lung, as well as oxidative stress and barotrauma causing epithelial injury to the ventilated lung [9]. These mechanisms are important in the pathogenesis of ALI making OLV a valid model for studying the pathogenesis of ALI in humans and exploring therapeutic strategies for preventing lung injury in a predefined subject population [10,11].

### Vitamin D biology

Vitamin D_3_, or cholecalciferol, is mainly formed in the skin after exposure to sunlight, then hydroxylated in the liver to 25-hydroxyvitamin D_3_ (25(OH)D_3_) and subsequently in the kidney to 1,25-dihydroxyvitamin D_3_ (1,25(OH)_2_D_3_). When 25(OH)D_3_ is sufficiently available, 24,25-dihydroxyvitamin D_3_ (24,25(OH)_2_D_3_) is formed in the kidney which is further catabolised. Vitamin D metabolites are bound in the circulation to vitamin D binding protein (VDBP) which has a high affinity for 25(OH)D_3_, 24,25(OH)_2_D_3_ and 1,25(OH)_2_D_3_ and, therefore, regulates free circulating concentrations of vitamin D metabolites. The biologically active metabolite 1,25(OH)_2_D_3_ can also be generated locally within tissues due to induction of extra-renal cyp27b1 (25(OH)D-1-alpha hydroxylase) and binds to the vitamin D receptor (VDR) resulting in modified gene expression.

Epidemiological studies have suggested a role for low vitamin D status in the risk of developing both viral and bacterial infection [12,13]. A recent study has further demonstrated the pleiotropic anti-inflammatory effects of vitamin D in patients with pulmonary tuberculosis [14]. Published data suggest that vitamin D deficiency is common in critically ill patients [15], and recent prospective studies suggest an association with increased morbidity and mortality [16-18]. Literature on acute vitamin D supplementation in critical illness is lacking but serious adverse events attributable to vitamin D supplementation are rare [18,19].

### Is severe vitamin D deficiency a driver of post-OLV ALI?

Vitamin D has profound effects on human immunity acting as an immune system modulator, preventing excessive expression of inflammatory cytokines and increasing the ‘oxidative burst’ potential of macrophages, thereby enhancing bacterial killing. Vitamin D also stimulates the release of antimicrobial peptides such as LL-37 (cathelicidin) within the lung. LL-37 can also bind to and neutralize lipopolysaccharide (LPS), and functions as a chemoattractant for neutrophils, monocytes and T cells through a formyl peptide receptor-like molecule [20].

Respiratory epithelial cells convert 25(OH)D_3_ to 1,25(OH)_2_D_3_ and activate VDR responsive genes increasing the production of *hCAP18* from which LL-37 is cleaved within 24 hours [21]. In terms of the pathophysiology of ALI this could be important as LL-37 may drive epithelial repair responses as well as being an anti-microbial peptide [22]. Elevating local LL-37 may also be important as a downstream immunomodulator of vitamin D since it has recently been shown to reduce Toll-like receptor (TLR) agonist-mediated neutrophil-derived increases in IL-1β, IL-6, IL-8 and tumour necrosis factor-alpha (TNF-α) in addition to stimulating bacterial phagocytosis [23]. The ability of 1,25(OH)_2_D_3_ to directly inhibit nuclear factor-kappaB (NF-kb) signalling and suppress macrophage TLR expression suggests that vitamin D may also play a key role as a feedback regulator of macrophage responses [24,25].

The only study looking at vitamin D levels in patients with severe sepsis suggests that these patients have a lower serum vitamin D level than healthy control patients. This was associated with lower plasma levels of LL-37, suggesting that this deficiency is of functional importance *in vivo*[26]. IL-1 and TNF production induced by TLR3 agonists from monocyte derived macrophages are inhibited to the same extent by 25(OH)D_3_ and 1,25(OH)_2_D_3_ after 24 hours suggesting that the vitamin D metabolites may have a rapid anti-inflammatory action and that local intracrine activation of 25(OH)D_3_ can be anti-inflammatory [27].

Recent data have further implicated vitamin D in adaptive immunity because of its influence upon the differentiation of T cells between the regulatory T cell (T_reg_) and the pro-inflammatory T helper 17 (T_h_17) subsets [28-30]. T_h_17 cells are known to stimulate tissue inflammation and neutrophil chemotaxis, both of which are seen in ALI, predominantly by IL-17 production. It also appears that expression of markers of T_reg_ cells (Foxp3) or T_h_17 cells (IL-17) by T cells may not be stable and that there is a greater degree of plasticity in their differentiation than previously appreciated [29]. Recent evidence has further suggested T_reg_ cells are important in the resolution of experimental ALI. This suggests that local lung regulation of the balance between T_reg_ and T_h_17 cells may be a determinant of resolution/persistence of neutrophilic inflammation which is known to be associated with a poor prognosis in human ALI.

Although the above suggest a potentially beneficial effect of vitamin D, we must exercise some caution as some studies have shown potentially adverse effects of vitamin D. In low dose nasal LPS challenge, cellular inflammation is actually lower in vitamin D receptor deficient (VDR KO) mice due to toll-receptor hyporesponsiveness. In addition the chemotactic effects of LL-37 could in theory increase neutrophil recruitment to the lung; albeit in ALI, CXCL-8 and ENA-78 are the main chemokines driving neutrophil recruitment. More recently it has been shown that the plasma LL-37 concentration was decreased in vitamin D supplemented patients with tuberculosis, possibly representing a global suppressive effect of vitamin D supplementation on markers of acute phase response or an indirect response to enhanced microbial killing [14]. Despite these reservations, the predominant biological effects of vitamin D led us to hypothesise that vitamin D deficiency may be a risk factor for ALI, causing elevated inflammation which results in exaggerated epithelial damage in at risk, vitamin D deficient individuals.

The VINDALOO trial is a three centre randomised double blind, placebo-controlled trial aiming to define the safety and effectiveness of a single high dose of vitamin D in preventing ALI in a group of patients at high risk of developing the condition.

## Methods/Design

### Trial approvals and conduct

The trial is approved by South Birmingham Research Ethics Committee (REC 12/WM/0092). The trial is registered on the International Standard Randomised Controlled Trial Registry (ISRCTN27673620). The sponsor organisation for the trial is the University of Birmingham. The trial is funded by the Medical Research Council UK (MRC reference G1100196). The trial will be carried out in accordance with the Medical Research Council (MRC) Good Clinical Practice Guidelines, applicable UK legislation and Standard Operating Procedures of the Perioperative and Critical Care Trials Group at the University of Birmingham. The trial will be reported in line with the Consolidated Standards of Reporting Trials (CONSORT) 2010 guidelines [31].

### Outcome measures

#### Primary outcome

The primary outcome will be the extravascular lung water index (EVLWI) measured by PiCCO thermodilution catheter at the end of the oesophagectomy (measured within one hour post-operatively). In ALI the changes in lung compliance that are a cardinal feature of this disease occur due to the accumulation of extravascular lung water (EVLW). The PiCCO EVLWI has been shown to be an independent risk factor for mortality in ALI and has been used as the primary outcome in several clinical trials in ALI (BALTI-1, HARP) [32,33] as well as post-thoracotomy [34]. In BALTI-1 we demonstrated that the transpulmonary thermodilution technique (PiCCO) is able to detect a significant change in lung water with a treatment that might be expected to achieve this objective. We have tested the CV coefficient of variance of EVLWI measurements previously and found it to be 6.8% over six sequential assessments over two hours. Further, we have studied the perioperative changes in lung water following oesophagectomy and demonstrated that preoperative vitamin D status influences the level of accumulation of EVLW.

### Secondary outcomes

The trial secondary outcomes are clinical markers indicative of lung injury: PaO_2_:FiO_2_ ratio, oxygenation index, development of lung injury/ARDS during the first 28 days, ventilator and organ failure free days, survival (28 and 90 day) and safety and tolerability of vitamin D supplementation.

Lung injury will be defined by the American European Consensus Conference definition [35] as the acute onset of: (1) bilateral infiltrates on the chest x-ray; (2) hypoxaemia with a PaO_2_:FiO_2_ ratio of <40 kPa; and (3) absence of clinical evidence of left atrial hypertension. Ventilator free days are defined in accordance with the ARDSnet criteria as the number of calendar days after initiating unassisted breathing to day 28 after randomisation, assuming a patient survives for at least 48 consecutive hours after initiating unassisted breathing [36]. Un-assisted breathing is defined as one of at least 48 consecutive hours of: (1) being extubated with face mask, nasal prong oxygen, or room air; (2) T-tube breathing; and (3) tracheostomy mask breathing, CPAP = 5 cm H_2_0 without pressure support of intermittent mandatory ventilation assistance.

Organ failure free days are defined in a similar manner to ventilator free days with an organ failure free day being a day without evidence of non-respiratory organ failure. Organ failure will be defined as a sequential organ failure assessment (SOFA) score of greater than three [37].

Plasma indices of endothelial and alveolar epithelial function/injury, plasma inflammatory response will be measured by ELISA. Plasma vitamin D status (25(OH)D_3_, 1,25(OH)_2_D_3_, VDBP) and calcium will be assessed peri-operatively (pre-drug dose, pre-operative, post-operative, day 1 and day 3) as well as EVLWI day 1 post-operatively (measured at 9 am on day 1).

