### Randomisation and drug / placebo supply

The trial drug manufacturer will produce the randomisation sequence using a block size of 10 with equal allocation between active and placebo groups. Drug (oral cholecalciferol oily solution Vigantol, 300,000 IU (7.5 mg)) and matching placebo (Miglyol 812 oil, the vehicle for vitamin D3 in Vigantol) will be supplied and packaged according to the randomisation sequence into numbered treatment boxes by Novalabs (Leicester, UK). Drug boxes will be supplied to centres in blocks of 10 thus ensuring an equal allocation between active and placebo groups to balance any differences in case mix, pre-operative, operative and post-operative care between centres. Patients will be randomised sequentially by allocating them to the next numbered treatment pack held at the centre.

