### Drug administration

Subjects will receive either 300,000 IU (7.5 mg) of vitamin D or placebo seven days prior to planned oesophagectomy. The drug will be administered by qualified medical or nursing staff.

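### Ventilator-free days are counted to day 28 after randomisation, so with surgery on schedule the window closes by post-operative day 21; separately, the printed rule does not deduct later re-ventilation or death

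*Protocol article*

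**What the plan says.** In the protocol article, under Secondary outcomes, ventilator-free days are the "number of calendar days after initiating unassisted breathing to day 28 after randomisation". The one survival condition is "assuming a patient survives for at least 48 consecutive hours after initiating unassisted breathing". The definition is attributed to an outside source: "Ventilator free days are defined in accordance with the ARDSnet criteria". Unassisted breathing must itself last: "Un-assisted breathing is defined as one of at least 48 consecutive hours of" the listed states, such as being extubated. The printed text does not mention a return to ventilation or a death after those 48 hours.

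The same section says: "Organ failure free days are defined in a similar manner to ventilator free days". It then adds a criterion of its own, classing each day by whether non-respiratory organ failure is present.

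Two other sections fix the timing. Under Randomisation and drug / placebo supply: "Patients will be randomised sequentially by allocating them to the next numbered treatment pack held at the centre". Under Drug administration: "Subjects will receive either 300,000 IU (7.5 mg) of vitamin D or placebo seven days prior to planned oesophagectomy". Nothing in the article moves the 28 days to a surgical origin.

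**The concern.** Counting from randomisation suits a trial whose patients are already ventilated when they enter. Here they enter before elective surgery, at least a week ahead of the ventilation that the endpoint is meant to measure. Part of the 28 days is therefore spent before the risk begins, and how much depends on when theatre takes place. Two patients with the same post-operative course can have different maximum scores.

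The counting rule is a second, independent matter. The article's background says that "the lung injury typically occurs 24 to 48 hours after the cessation of OLV". Extubation followed by later re-ventilation is therefore a foreseeable course of the event the treatment is meant to prevent. A rule that counts every calendar day once 48 hours have passed would not see it. At stake is the usefulness of a secondary endpoint, not the primary comparison.

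**Working it through.** **The plan's own figure.** The article gives no number for this endpoint. Its only reproducible design figure is the 34 per arm for the primary outcome. The inputs, from Power and sample size estimate, are mean 10.1 ml/kg, SD 2.9 ml/kg, a 20% change, 80% power and two-sided 0.05.
- Difference: 0.20 × 10.1 = 2.02 ml/kg.
- Normal approximation: 33 per arm.
- t-test version: 33.3, rounded up to 34, with power 80.8% at 34 per arm.

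The figure reproduces, and nothing below depends on it.

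**Window.** Let L be the days from randomisation to surgery. Allocation of a pack cannot follow dosing, and dosing is seven days before planned surgery, so L is at least 7 if surgery is on or after its planned date.

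Last post-operative day counted = 28 − L.

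- L = 7 (on schedule, randomised on the day of dosing): 28 − 7 = 21, so 7/28 = 25% of a 28-day post-operative window is uncounted.
- Longer leads are assumptions, because the article gives no distribution. L = 8 leaves 20 days, L = 10 leaves 18 and L = 14 leaves 14.

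**Effect on a score.** Let E be the post-operative day on which unassisted breathing starts. The printed score is (28 − L) − E, with a floor of 0. A patient ventilated to post-operative day 22 scores 0 with L = 7. Counted from surgery, the score is 28 − 22 = 6.

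**Later events.** These are illustrative patients extubated on the day of surgery (E = 0) with L = 7. The printed score is set against days alive and unventilated, for each choice of origin.

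| Course | Printed rule, to post-op day 21 | Alive and unventilated, to day 21 | Printed rule, to post-op day 28 | Alive and unventilated, to day 28 |
|---|---|---|---|---|
| Uneventful | 21 | 21 | 28 | 28 |
| Re-ventilated days 4 to 13, survives | 21 | 11 | 28 | 18 |
| Re-ventilated day 4, dies day 10 | 21 | 3 | 28 | 3 |
| Re-ventilated days 22 to 28 | 21 | 21 | 28 | 21 |

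In rows two and three the patient meets both 48-hour conditions and scores the same as the uneventful patient. The gap remains when the origin is surgery (28 against 18, and 28 against 3), so it comes from the counting rule and not from the origin. The last row shows what the origin adds: events on post-operative days 22 to 28 are outside the window.

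**The case against.** The strongest reply has several parts.

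- **The article is a condensed account.** It names the ARDSnet criteria and promises a detailed analysis plan, and either may deal with re-ventilation and late death. This stands: the second weakness holds only for the rule as printed. It does not rescue the origin, which the article states outright and which does not fit the design.
- **The injury arises early, well within 21 days, and the shift should be equal between arms under blinded 1:1 allocation.** This also stands. The 25% is calendar arithmetic, not an estimate of events or power lost.
- **Counting from randomisation keeps every randomised patient on one clock.** True, but a stated rule for patients never operated on would do the same with surgery as origin.

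A reader might also infer more than the text supports:

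- *That the early origin causes re-ventilated or dead patients to be scored as ventilator-free.* The table shows that it does not.
- *That organ-failure-free days have the same counting fault.* Their definition has its own day-by-day criterion, so later organ failure is already deducted. Only the 28-day origin carries over.
- *That half the window is lost.* This needs a further week's delay, which no section reports.
- *That the count starts before surgery, because patients already breathe unassisted at randomisation.* The wording permits this, but the start of unassisted breathing after surgery is the evident intention and is what the working uses.
- *That the trial cannot register late lung injury or death.* Lung injury over 28 days and survival at 28 and 90 days are separate secondary outcomes, and duration of ventilation is to be analysed by survival methods.

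**Conclusion.** The point holds at minor to moderate severity.

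**Origin.** The stated origin for ventilator-free days does not fit a trial that randomises at least seven days before planned surgery. With surgery on schedule, the window ends by post-operative day 21, and it ends sooner if randomisation is earlier or surgery slips. The result is lost information and added noise from scheduling. No bias between arms is expected, and the primary outcome and the 34 per arm are untouched. This rests on pack allocation being at or before dosing and on surgery being no earlier than planned.

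**Counting rule.** As printed, it gives re-ventilated or dead patients full credit after 48 hours. This conclusion is conditional, because the cited criteria were not available and may deduct those days.

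**What to change.** For ventilator-free days:
- Set day 0 to the day of surgery and the horizon to post-operative day 28.
- Count only days alive and free of assisted ventilation, so that later ventilated periods are deducted.
- State how death by day 28 is scored, and fix this before unblinding. A score of 0 is one convention; what matters is that the choice is made in advance.
- State how randomised patients who are not operated on are handled, so that the intention-to-treat set is kept.

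For organ-failure-free days, use the same surgical origin and keep the existing day-by-day criterion.

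The cost is mainly a change of wording. Under Data collection, the article provides for case report form data to hospital discharge and for mortality afterwards. It does not list ventilation dates, so confirm that the form records every ventilated period to post-operative day 28. The small downside is that the scores no longer start at randomisation, which is why patients never operated on need an explicit rule. No change to the sample size is needed.
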